## 4.3 Screen Failures and Rescreening (Cohort A and B)

Screen failures are subjects who do not fulfill the eligibility criteria for the study and therefore must not be assigned treatment or randomization. These subjects should have a reason for study withdrawal recorded as “eligibility criteria not fulfilled” (subject does not meet the required inclusion or meets any of the exclusion criteria). This reason for study withdrawal is only for screen failures. Subjects who fail screening will have the following information collected: demography, eligibility criteria including reason for screen failure, and AEs.

Screen failures for reasons other than use of prohibited medications(s) may be discussed with the Medical Monitor to determine if rescreening is appropriate. Subjects may be rescreened once with approval from the Medical Monitor; rescreening will require a new subject number.

Subjects who were considered screen-failures due to their PCr recovery rate constant (< 50 seconds) provided their CFQ-11 score is ≥ 8 and meet the rest of the eligibility criteria will be rescreened and included in Cohort B.

## 4.4 Subject Enrollment (Cohort A and B)

A subject will be considered for enrollment when the subject provides written informed consent, or reconsent as applicable for local policies and regulations, and when the subject has met all inclusion criteria and none of the exclusion criteria. Further information about the requirements for written informed consent is provided in Section 8.1.1.1.

A subject will be considered enrolled when he or she has met all eligibility criteria, has been selected to participate in the study, and has agreed to participate and has been randomized.

Approximately 40 subjects (Cohort A), and approximately10 subjects (Cohort B) are to be enrolled in this study.

## 4.5 Subject Withdrawal (Cohort A and B)

While subjects are not obligated to state the reason for withdrawal, the reasons for withdrawal or failure to provide a reason must be documented by the PI on the relevant electronic case report form (eCRF). Every effort should be made by the PI to follow subjects who withdraw from the study for at least 30 days.

An enrolled subject who withdraws consent or is withdrawn from the study per the PI’s discretion before completing all study activities per protocol will be considered an early termination.

### 4.5.1 Withdrawal from study participation

Participation in this study is voluntary, and a subject may withdraw consent and discontinue participation in this study at any time at his/her own request without prejudice or consequence. The PI may also, at his/her discretion, discontinue the study treatment and/or withdraw the subject from the study at any time (eg, safety, behavioral, or administrative reasons). If a subject withdraws from the study, they will be instructed to return all unused study drug to the study site or central location for study drug accountability. Samples not taken are to be destroyed, and the PI must document this in the site study records.

A subject may withdraw from study participation (study drug and study assessments) or be withdrawn from study participation by the PI for reasons including but not limited to any of the following:

- Subject’s stable chronic medical condition(s) deteriorates and/or clinically significant adjustments/titrations in their stably maintained medical regimen are made during the study;
- Subject independently withdraws consent from the study;
- Subject has 1 or more medical reasons considered clinically significant by the subject, PI, and/or Sponsor, which may include an intercurrent illness, condition, AE, and/or reasons unrelated to the study;
- Protection of the subject’s health or the integrity of the study;
- Subject failure to comply with study requirements (eg, failure to properly consume the study drug [<80% compliance] failure to comply with other protocol-specific assessments); or
- Subject is lost to follow-up (Section 4.5.4).

Early discontinuation of study drug alone is not a criterion for withdrawal of consent for participation in the study.

### 4.5.2 Withdrawal from study drug only

A subject may withdraw from study drug and remain in the study by continuing all study assessments for reasons, including but not limited to any of the following:

- If a subject experiences an SAE judged by the PI to be possibly, probably, or definitely related to the study drug, the subject may be discontinued from the study drug and will not restart treatment but may remain on study for continued follow-up until resolution of the SAE; the subject will continue his/her consent to participate in the study for follow-up only (eg, for continued collection of AE information);
- Development of an AE(s). AEs leading to discontinuation of the study drug should be followed until the AE is resolved;
- Inability to self-administer study drug orally. The subject will be discontinued from the study drug but may remain on study for continued follow-up;
- Protection of the subject’s health or the integrity of the study;
- Grade 3 or higher and related to study drug or Grade 4 or higher regardless of causality as defined by the Common Terminology Criteria for Adverse Events (CTCAE) version 5.0 (see Section 6.7.3)

### 4.5.3 Handling of discontinuation of study drug and study withdrawals

If the PI discontinues a subject from study drug due to development of an AE, every effort should be made to complete the ET procedures as outlined in the Schedule of Assessments (SOA;

APPENDIX 1; APPENDIX 2) as soon as possible after the last dose of study drug and to monitor the subject for resolution of the AE or for the development of new AEs for 4 weeks after the last dose of study drug.

If a subject withdraws consent or is terminated for any other reason, every effort should be made to complete the ET assessments as outlined in the SOA (APPENDIX 1; APPENDIX 2).

The reason for subject withdrawal must be documented in the eCRF.

Subjects who discontinue or withdraw from the study will not be replaced.

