# 3 STUDY DESIGN

## 3.1 Overall Study Design

###### Cohort A

This is a minimum of one center, randomized, double-blind, placebo-controlled, pilot clinical study in the United Kingdom (Figure 1). The study will evaluate the efficacy and safety of AXA1125 in subjects with fatigue-predominant PASC (>12 weeks after initial infection).

The total study duration for each subject will be approximately 9 weeks. This study will comprise a Screening Period of up to 4 weeks, a Treatment Period of up to 4 weeks, and a Follow-up Period of 1 week.

After obtaining informed consent, subjects will be screened, and approximately 40 eligible subjects

(approximately 20 subjects per arm) will be randomized in a 1:1 ratio to receive BID oral administration of 33.9 g AXA1125 or a placebo. Doses will be self-administered on Days 1 to 28, inclusive. Subjects will have clinic visits on Day 1 and Day 28, as well as telephone visits on Day 14 and 1 week after completion of study product administration. Note: Doses should be self-administered at the clinic visit on Day 1 and Day 28 or End of Treatment (EOT)/Early Termination (ET).

The primary efficacy endpoint is the mean change from baseline at Week 4 in the PCr recovery rate following moderate exercise, as assessed by 31P-MRS, which will be evaluated at Screening and EOT/ET (Visit 4). Additional endpoints for assessment of muscle function, safety, tolerability, and exploratory efficacy endpoints will be assessed during the study

Details of randomization will be provided in the Randomization Plan and Interactive Response Technology (IRT) system.

Figure 1 Study Schematic - Cohort A

[figure not shown]

BID=twice daily; D=Day; MRS=magnetic resonance spectroscopy; PRO=patient-reported outcomes.

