# 7 STATISTICAL CONSIDERATIONS

## 7.1 Sample Size Estimation (Cohort A and B)

**Cohort A**

The sample size calculation is based on the primary efficacy endpoint, the mean change from baseline at Week 4 in the PCr recovery rate. Based on literature review, the standard deviation (SD) of both the AXA1125 and the placebo group is assumed to be 10 seconds. To detect a clinically meaningful difference of 10-second improvement, approximately 32 subjects will provide 80% power at a 2-sided, 5% significance level. Assuming 20% dropout rate, approximately 40 subjects (20 subjects per arm) will be enrolled in this study.

This sample size will also allow for a general assessment of safety and tolerability of AXA1125 in this population. **Cohort B** Approximately 10 subjects (5 subjects per arm), who were considered screen-failures for Cohort A due to their PCr recovery rate constant (< 50seconds) provided their CFQ-11 is ≥ 8 and they meet all the eligibility criteria will be enrolled in this Cohort.

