## 7.4 Statistical Methods (Cohort A and B)

### 7.4.1 General approach

Descriptive statistics for continuous variables will include the number of subjects with data to be summarized, mean, SD, median, and range (minimum, maximum).

All categorical/qualitative data will be presented using frequency counts and percentages.

The statistical methods for comparison of each endpoint and complete missing imputation methods will be detailed in the Statistical Analysis Plan (SAP), which will be developed and completed prior to database lock.

There will be no multiplicity adjustment and all analyses will be performed at the 2-sided 0.05 level of significance.

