### 7.4.3 Handling of dropouts/missing data

For binary endpoints, both worst-case and observed-case methods will be applied as the missing imputation method. Worst-case method is defined as subjects with missing data due to any reason will be considered as not meeting the endpoint. Observed-case imputation method is defined as subjects with missing data will not be included in the analysis. For continuous endpoints, both single and multiple missing imputations will be applied.

To address each of potential intercurrent events, the strategies will be detailed in the SAP, if appropriate.

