### 7.4.7 Efficacy analyses (Cohort A and B)

#### 7.4.7.1 Primary and key secondary efficacy endpoint analyses

The categorical endpoints will be analyzed using the Chi-square test. Subgroup analyses, such as by gender, may be performed.

Continuous endpoints will be analyzed using the analysis of covariance models adjusted for the baseline value. Mixed model repeated measures models will be applied as sensitivity analyses.

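### Sections 4.5.1 to 4.5.3 conflict on whether subjects who stop study drug are assessed at Week 4, and the MMRM named as sensitivity analysis tests nothing for the single-visit primary endpoint

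*Protocol*

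**What the plan says.** - **Endpoint and timing.** Section 2.3.1.1 sets the primary endpoint at Week 4. Section 3.1 has PCr recovery "as assessed by 31P-MRS, which will be evaluated at Screening and EOT/ET (Visit 4"). Appendix 1 gives EOT and ET one shared visit, nominally Day 28 with a window of 3 days either side.
- **Population.** Section 7.2.1 makes the ITT set (randomized and dosed, analysed in the assigned arm) primary for efficacy.
- **Stopping drug only.** Section 4.5.2: "A subject may withdraw from study drug and remain in the study by continuing all study assessments". An adverse event is one of the listed reasons. The item on related serious events, however, narrows the subject to follow-up such as collection of adverse event data.
- **Stopping for an adverse event.** Section 4.5.3: when the investigator discontinues drug for an adverse event, "every effort should be made to complete the ET procedures as outlined in the Schedule of Assessments", without delay once dosing ends, followed by four weeks of adverse event monitoring. ET assessments are also sought from subjects who withdraw consent or are terminated for other reasons.
- **Poor compliance.** Section 4.5.1 lists "failure to properly consume the study drug [<80% compliance"] among the reasons for which a subject may be withdrawn from both drug and assessments. It adds that stopping drug early does not by itself count as withdrawing consent.
- **Analysis.** Section 7.4.7.1 specifies baseline-adjusted ANCOVA for continuous endpoints and adds: "Mixed model repeated measures models will be applied as sensitivity analyses". Section 7.4.3 says: "For continuous endpoints, both single and multiple missing imputations will be applied". It leaves intercurrent-event strategies to the SAP.

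**The concern.** Two separate weaknesses meet at the primary endpoint.

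The first is data collection. A site whose investigator stops drug for an adverse event finds one section that keeps the subject in all assessments and another that calls for the ET visit at once. Because ET and EOT are the same visit and PCr has no other post-baseline scan, following Section 4.5.3 can make an early scan the subject's only one. A subject withdrawn from assessments for poor compliance may have an early ET scan or none. An analysis plan written later can decide how to label an early value, but it cannot recover a Day 28 scan that was never taken.

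The second is the check on the result. A sensitivity analysis should change an assumption that the main analysis makes. For PCr and 6MWT distance the MMRM changes nothing, so agreement between it and the ANCOVA would look like reassurance but be guaranteed by algebra.

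If stopping or poor compliance depends on treatment, the comparison drifts from all treated subjects at Week 4 towards those who tolerated the product, and the MMRM could not show it.

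**Working it through.** **1. The plan's own figure.** Section 7.1: "To detect a clinically meaningful difference of 10-second improvement, approximately 32 subjects will provide 80% power at a 2-sided, 5% significance level", with SD 10 s per arm and 20% dropout. Normal approximation: n per arm = 2 × (1.96 + 0.84)² × (10/10)² = 15.7, so 16 per arm and 32 in all. Then 32 / (1 − 0.20) = 40. Power at 16 per arm is 0.807 (0.781 with the noncentral t). The stated 32 and 40 reproduce and are not in dispute. They allow for 8 of 40 subjects without a usable value.

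**2. The sections side by side, for a subject whom the investigator stops for an adverse event.**

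| Section | Direction | PCr scan that follows |
|---|---|---|
| 4.5.2 | may stay and continue all assessments | Day 28±3 |
| 4.5.2, related serious event | may stay for follow-up | not clear |
| 4.5.3 | ET procedures promptly after last dose | early, and shares Visit 4 |

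For compliance below 80%, Section 4.5.1 permits, but does not require, withdrawal from assessments. The scan is then an early ET reading or absent.

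The route will be used: Section 6.7 says that subjects with a related severe adverse event should be discontinued. The timing can matter too. Section 1.5.2.1 gives median onset of selected gastrointestinal events in Study AXA1125-003 (45.2 g/day) as 12.5 to 25.5 days. The Visit 4 window opens at Day 25. Onset is not the stopping date, so this shows only that an ET visit could fall well before the window.

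**3. MMRM with one post-baseline visit.** With several visits, an MMRM borrows information about a missing visit from the subject's other post-baseline values through the covariance matrix. With one visit that matrix is a single variance. A subject without the value contributes nothing, generalised least squares reduces to ordinary least squares, and the REML variance is the residual sum of squares over its degrees of freedom. That is ANCOVA on the observed subjects. Entering baseline as a response with a common mean does not help: the likelihood factorises and the maximum likelihood treatment coefficient is unchanged.

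Numerical confirmation: 500 simulated trials, 40 subjects, 8 missing at random (assumed baseline mean 70 s, SD 14 s, residual SD 9 s). The largest difference between the two treatment estimates was 4 × 10⁻¹⁴ s, and between standard errors about 10⁻⁷ s, which is rounding and optimiser noise.

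This holds for PCr (Section 6.8.1) and 6MWT distance (Section 6.8.3). It does not hold for CFQ-11, measured at Day 14 and Week 4. Lactate is left out because Section 6.8.4 also repeats capillary readings within a visit.

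**4. Multiple imputation.** Under missing at random with only baseline and arm in the imputation model, it targets the same estimate as complete-case ANCOVA. It adds something only with informative extra variables or a different assumption about the missing values. Day 14 CFQ-11 is the obvious extra variable, but Section 1.5.2.3.2 reports that change in fatigue did not correlate with change in PCr at Week 4.

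**5. Illustrative size.** Let p be the proportion in an arm without a Week 4 value and δ how much worse, in seconds, those subjects would have been than completers. Each full-arm mean is worse than its completer mean by p × δ, so the completer difference is overstated by (p_active − p_placebo) × δ. Take δ = 5 to 10 s (assumption).

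- Low end: Section 1.5.2.1 reports 2 discontinuations among subjects with gastrointestinal events in Studies AXA1125-002 and -003, and 61 NAFLD subjects. Assuming both were on AXA1125 and none stop on placebo, 2/61 = 3.3%. Then 0.033 × 5 = 0.16 s and 0.033 × 10 = 0.33 s.
- High end: the planned 8 losses split 6 and 2 (assumption), so 6/20 − 2/20 = 0.20. Then 0.20 × 5 = 1 s and 0.20 × 10 = 2 s.

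The range is about 0.2 to 2 s, or 2% to 20% of the 10 s target.

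**The case against.** The other side has several good points.

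- **Scope of the ET rule.** A reader might infer that everyone who stops drug goes straight to ET and so lacks a Week 4 reading. The Protocol does not say that. Prompt ET covers discontinuation by the investigator for an adverse event; Section 4.5.2 allows others to continue all assessments, and ET subjects do get a scan, only early. This stands, and limits the point to a conflict between sections.
- **Compliance.** The 80% item in Section 4.5.1 is permissive. It opens a route to missing data but does not mandate one.
- **Estimand.** Section 7.2.1 assigns subjects to their randomized arm. It might be read as fixing a treatment-policy estimand, but it does not, and Section 7.4.3 leaves intercurrent events to the SAP. Windowing of ET values is also normal SAP content. What the SAP cannot supply is the scan itself.
- **MMRM as safeguard.** The Protocol never presents MMRM as its missing-data method; Section 7.4.3 names single and multiple imputation. A redundant analysis biases nothing, and MMRM has real content for CFQ-11. Even so, Section 7.4.7.1 names it as the sensitivity analysis for all continuous endpoints, and for the primary one it is empty.
- **Evidence of differential stopping.** The 25% diarrhoea at 67.8 g/day in Section 1.5.2.1 comes from an open-label study in another population, and few subjects with gastrointestinal events stopped. Differential stopping is plausible, not shown.
- **Single imputation.** A reader might try to put a figure on the resulting test size. The method is not named, so no figure is supported.

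**Conclusion.** The point holds in two parts. First, Sections 4.5.1 to 4.5.3 do not agree on whether a subject who stops drug, or complies poorly, is assessed at Week 4, and the shared EOT/ET visit means that such a subject may have only an early PCr reading or none. Second, MMRM is identical to complete-case ANCOVA for PCr and 6MWT distance, so it is not a sensitivity analysis for the primary endpoint. The planned multiple imputation fills that gap only if it uses more than baseline and arm under missing at random.

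The second part is a matter of algebra and rests on no assumption beyond the visit schedule. The size of any bias is unknown from the documents. The 0.2 to 2 s range is illustration only, resting on an assumed 3 to 20 percentage point difference in stopping and stoppers 5 to 10 s worse. The documents do not support a claim that the primary result will be biased. They do support correcting the plan, because a Week 4 scan that was not taken cannot be recovered.

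**What to change.** 1. **Reconcile Sections 4.5.1, 4.5.2 and 4.5.3** on assessments, leaving the rules for stopping drug and the safety ET procedures as they are. Subjects who stop drug or comply poorly, have not withdrawn consent and are able to attend should have the Visit 4 efficacy assessments at Day 28±3.
2. **State that an early ET value is not analysed as Week 4.** It can be listed as an ET value.
3. **Section 7.4.7.1:** keep MMRM for CFQ-11 (Day 14 and Week 4). For PCr and 6MWT distance, replace it with control-based or delta-adjusted multiple imputation, so that the sensitivity analysis varies the assumption about subjects without a Week 4 value.

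The cost is a short amendment and matching SAP text. The burden falls on a few off-drug subjects who return at Day 28 for the scan, with its exercise and 6-hour fast, and the walk test. If an ET scan has already been done, the Day 28 scan is an additional one. The planned allowance of 8 losses in 40 suggests that the number is small, and those who withdraw consent or cannot attend are not asked to return.

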### 4.5.4 Lost to follow-up

A subject is considered lost to follow-up when he/she repeatedly fails to return to the site for scheduled visits and the site is unable to contact the subject.

If a subject fails to return to the site, the study site personnel must:

- Attempt to contact the subject and reschedule the missed visit as soon as possible.
- Counsel the subject on the importance of maintaining the assigned visit schedule.
- Ascertain whether the subject wishes to and should continue in the study.

Before a subject is considered lost to follow-up, the PI or designee must make 3 attempts to regain contact with the subject. These contact attempts should be documented in the subject’s source documents.

Should the subject continue to be unreachable, only then will he/she be considered to have withdrawn from the study with the primary reason of “Lost to follow-up”.

# 5 STUDY INTERVENTIONS (Cohort A and B)

## 5.1 Study Drug

### 5.1.1 AXA1125

AXA1125 is an orally active mixture of 5 specific AAs (leucine, isoleucine, valine, arginine, and glutamine) and Nac (an AA derivative). The AA composition within AXA1125 is described in Table 1.

###### Table 1 Amino Acid Composition Within AXA1125

| **Ingredient** | **Ingredient Function** | **Unit Dosage Dry Weight (g)** |
| --- | --- | --- |
| L-Leucine | Active | 2.000 |
| L-Isoleucine | Active | 1.000 |
| L-Valine | Active | 1.000 |
| L-Arginine HCl^1^ | Active | 3.628 |
| L-Glutamine | Active | 4.000 |
| N-acetyl-L-cysteine | Active | 0.300 |

HCl=hydrochloride

Note: Total may be >100% due to rounding off.

^1^ Arginine is sourced as arginine monohydrochloride; 3.628 g of L-Arginine HCl equals 3.001 g of L-Arginine.

The excipients within AXA1125 include citric acid, soybean lecithin, xanthan gum 180, sucralose, orange flavor, custard flavor, FD&C yellow no. 6, low-substituted hydroxypropyl cellulose NBD-022, colloidal silicon dioxide, magnesium stearate, and AAs without hydrochloride. The excipients and their respective concentrations were specifically chosen for AXA1125 and are designed to deliver a uniformly dispersed, orange-colored, and orange-flavored liquid suspension upon constitution with ~6 fluid oz of potable water.

The active pharmaceutical ingredients and excipients are compounded to produce a uniform dry powder blend for suspension and are provided as a unit dose sachet containing 11.3 g AAs. The container closure system for AXA1125 is a 5-layer

(paper/polyester/polyethylene/foil/polyethylene), heat-sealed, unit-dose, foil sachet. One end of the heat-sealed sachet is notched to provide an easy-tear opening for subjects.

Detailed information regarding AXA1125 formulation, constitution instructions, appearance, and storage requirements are described in the Pharmacy Manual.

